3. Men and women aged 18-65 years old. We are not enrolling younger children as they are not part of the Intensive Pain Rehabilitation Therapy program. 65 is our upper limit for age due to changes in blood flow on the MRI.

4. Eligibility will be assessed using the following questions: “(1) How long has back pain been an ongoing problem for you? and (2) How often has low-back pain been an ongoing problem for you over the past 6 months?” A response of greater than three months to question 1, and a response of “at least half the days in the past 6 months” to question 2 would meet the cLBP eligibility criterion.

5. Ability to speak English. We do not have the capacity, given the resources available in this proposal, to translate all course material and conduct groups into another language. We have previously enrolled Hispanic participants into other studies who were fluent in English, and expect to do this in the proposed study.

6. Low level of interoceptive awareness and habitual distraction as coping mechanism with pain. This is defined as:

a) MAIA summary score below the population mean score of 3.41.  The value of 3.41 is the mean value of a sample of primary care patients at Kaiser Permanente in a prior study.

b) the MAIA Non-Distraction score is below 2.91 [possible range 0-5].  The value of 2.91 is the mean value plus standard deviation in the same sample.^4^

This eligibility criterion was chosen to test the hypothesis that the MIET task will be able to increase interoceptive awareness in patients with chronic low back pain with below average interoceptive awareness and preference for distracting themselves from their pain experience.

7. Owning a smart phone: the task is smart phone-based.

Under NIH definition, all individuals under the age of 21 are considered children. Eligible participants who are 18 years of age or older will be recruited for this study. Younger children will not be included in this study because a pediatric sample may require different intervention approaches.

Exclusion Criteria:

1. Unable to provide informed consent.

2. A substance abuse, mental health, or medical condition that, in the opinion of investigators, will make it difficult for the potential participant to participate or that may need immediate changes in medical management that will affect study outcome measures. Such conditions may include cancer, liver failure, renal failure, pain conditions from inflammatory diseases (e.g. rheumatoid arthritis, ankylosing spondylitis, lupus), malignancies or abdominal aortic aneurysm, muscle weakness from radiculopathy. Radiculopathy or sciatic pain is NOT excluded as long as the condition is stable and does not lead to significant movement restrictions or <4/5 muscle weakness. Persons with significant substance abuse or mental health conditions that interfere with social functioning may be disruptive. Oher medical or mental health conditions that need immediate changes in management need to be addressed before starting the study so that more reliable baseline measurements can be made. Patients who may need assessment for potentially necessary surgical interventions may not be able to complete the study. Regular opioid prescription is not an exclusion if stabile over the past 3 months.

3. Spine related current or history of spine infection, spine tumor, vertebral fracture, cauda equina syndrome. Colorblindness or left handedness. Conditions would increase heterogeneity of the sample.

4. Blindness, severe vision problems, deafness, severe hearing problems, bipolar or manic depression and not taking medication, major depression, psychoses (major), a substance abuse condition, dementia, unable to get up and down from the floor. Condition might make it difficult to participate.

5. Some other serious medical conditions that may alter key study outcomes, including untreated hypothyroidism, renal failure, and cirrhosis. Conditions that may alter key study outcomes.

6. Involvement in a lawsuit related to their back. Complicated medico-legal issues that could lead to individuals having a financial incentive to not report improvement.

7. Involved in Worker's Compensation claim.

8. Pregnant, breast-feeding, or planning to get pregnant in the next 12 months or less than 3 months post-partum. Particular back problems than may be associated with pregnancy and delivery may confound study outcomes.

9. Lack of stable housing or plan to move out of the area within the next 6 months.

10. MRI-related exclusion criteria: Cardiac pacemaker, metal fragments in eyes/skin/body (shrapnel), subjects who have ever been a metal worker/welder; history of eye surgery/eyes washed out because of metal, aortic aneurysm clips, prosthesis, by-pass surgery/coronary artery clips, hearing aid, heart valve replacement, subjects with an I.U.D, a shunt (ventricular or spinal), electrodes, metal plates/ pins/screws/wires, or neuro/bio-stimulators (TENS unit), vision problems uncorrectable with lenses, claustrophobia; inability to lie still on one’s back for approximately 60 minutes; prior neurosurgery; older tattoos with metal dyes; unwillingness to remove nose, ear or face jewelry, braces or permanent dental retainers. Iron-containing metal parts in the body can potentially be dislocated by strong magnetic fields and preclude assessment with MRI.

11. Received a steroid or botox injection in or near the spine in the last 3 months. This may alter key study outcomes.

Subject Identification Method:

We plan to recruit both males and females. We anticipate that male/female ratio will match the gender, racial and ethnic composition of San Francisco county population.

at UCSF: UCSF saw 1,658 patients for cLBP in primary care during the past two years (data search 5/2017). The PIs  [name] and [name] are co-investigators in the NIH-funded BACPAC REACH study at the UCSF Spine Center. This study plans to enroll an internet cohort of 5,000 patients. Every 2 weeks, the REACH study manager will provide the SRA of the Mind your Pain study with a list of enrollees, which live in the Bay Area. Enrollees have consented to be contacted for other back pain-related studies. They will be invited by mail and e-mail and receive a flyer about the Mind your Pain (MyP) study with contact phone number and e-mail address.

at the VA: Potential participants will be recruited from the Intensive Pain Rehabilitation Program (IPRP), a clinical service offered to veterans with chronic pain at the SFVAMC. In addition, we will identify potentially eligible participants enrolled in research studies with [name] at the SFVAMC. For another study, the IPRP program is an established clinical program (Clinical Director [name]. is a co-investigator on the proposal) serves about 500 patients every year. If patients enrolled in IRPR have to wait for 8 weeks for their online therapy program they will be informed and invited by IPRP staff to participate in the MyP study. A MyP study flyer with contact phone number and e-mail address will be used.

at the UCSF Osher Center: Our institute is highly experienced in recruiting study participants. We will hang out flyers in its clinic space and may contact participants in prior studies who have consented to be contacted for further studies.

ResearchMatch.org will be utilized as a recruitment tool for this protocol. ResearchMatch.org is a national electronic, web-based recruitment tool that was created through the Clinical & Translational Science Awards Consortium in 2009 and is maintained at Vanderbilt University as an IRB-approved data repository. UCSF is part of the ResearchMatch network, so UCSF researchers are allowed to use this registry with IRB approval.

How it works: Anyone residing in the United States can self-register as a potential research volunteer on ResearchMatch.com. Once registered, volunteers’ coded information becomes part of a pool of data that researchers can search through when looking for people to contact about their studies. The researchers then send a recruitment message (attached to this submission) to potentially eligible volunteers through ResearchMatch's secure web system. After receiving the recruitment email from ResearchMatch, the volunteer can click a button to release their contact information to the researcher if they want to learn more about the study. All volunteer information is kept confidential until the volunteer decides to release it.

Determination of Eligibility:

After making initial contact with the subject and prior to enrollment, eligibility screening will be conducted by trained research staff. Due to the extensive nature of the eligibility screening, participants will be asked to give verbal consent (see section 10.7) before the screen is conducted. If a potential subject is interested in participating and provides verbal consent, he or she will be asked a series of eligibility questions. If he/she meets initial requirements for preliminary eligibility and is interested in participating, the potential participant will be invited and potentially scheduled for a zoom-based appointment with the study team at the UCSF Osher Center.

Eligibility will be determined after 2 steps: (1) Potential participants, which have heard or read about the study, will be screened by phone by the SRA. If passing eligibility criteria and after providing informed consent, (2) provisionally eligible potential participants will sign informed consent and then answer the MAIA online at home by Qualtrics. If their summary score is below the population mean score of 3.41 and the Non-Distraction score is below 2.91 [possible range 0-5], they are fully eligible and will be informed by phone and/or e-mail about their eligibility by the SRA. The value of 3.41 is the mean value of a sample of primary care patients at Kaiser Permanente in a prior study, and the value of 2.91 is the mean value plus standard deviation in the same sample.^10^ This eligibility criterion was chosen to test the hypothesis that the MIET task will be able to increase interoceptive awareness in patients with chronic low back pain with below average interoceptive awareness and preference for distracting themselves from their pain experience.

Potential participants enrolled in REACH have passed the same eligibility criteria applied to the Mind your Pain study except one: the below-average value of the MAIA summary and Non-Distraction scores. Once reached over the phone and after providing informed consent, these provisionally eligible potential participants will answer the MAIA online at home by Qualtrics or REDCap. They will be eligible with the same below-average scores defined above.

Initiation of Contact/Recruitment:

Investigator's colleagues in clinics (i.e. pain clinic; Osher Center clinic, Family Medicine Clinic, etc) may introduce study to potential participants and provide them with the study team's recruitment material(s) and/or contact information.

As outlined above, potentially eligible participants at UCSF and at the SFVAMC will be handed flyers for this study.

We will use the UCSF study website, UCSF recruitment tools, and social media (such as facebook adds).

We will use a telephone screening script, a recruitment letter, or e-mail template approved by UCSF-IRB.

All recruitment is done by trained research staff who are assigned to this study, using aforementioned recruitment methods as well as methods listed below. Subjects can either contact the study staff, or study staff may contact the subject. The study team will not initiate contact with subjects by telephone unless they have received permission from the potential subject to be contacted by telephone. Permission is provided verbally (in the case of provider referrals), implied or written (in the case of VA approved research mailings), or explicitly by the potential subject. Initial contact by the study team must be in-person (including by phone and/or zoom) or by mail, unless the subject initiates contact. Upon contact, subject will be given information about the study. They will then be asked if they are interested in participating and will be screened for eligibility.

Interested candidates who either 1) respond to recruitment solicitation and initiate contact with the study team via e-mail or phone or 2) who are approached by the study team directly will be given an overview of the study and its enrollment requirements and will be initially screened by an online screener and telephone. If a potential participant is interested and meets initial requirements for participation, he/she will be invited for a zoom appointment with a trained staff member (CRC) at the UCSF Osher Center or the PI. This appointment, which will take place via zoom, will entail meeting with trained research personnel (CRC) who will describe the study in detail, address any questions/concerns, and obtain informed consent for study participation.

Recruitment strategies: Recruitment methods and media may include flyers; in-person presentations; a study specific webpage; informational letters; print newsletters; press releases or advertisements in print, internet, television, and radio, public service announcements; public notice-board postings; contact with and referral from relevant clinicians; social media, pamphlets; informational sessions about the research. In clinical settings, care providers will also be given informational materials to distribute to potential candidates.

The above-mentioned recruitment strategies will also take place at social service agencies, community mental health clinics, community organizations/events, including local professional organizations, consenting support and recovery centers, local hospitals and healthcare systems, regional employee assistance programs, religious organizations, cultural centers, public transportation vehicles and stations, social clubs, and universities.

Any recruitment materials (fliers, brochures, etc.) that will be used will be submitted to IRB for approval prior to use.

My Chart Recruitment:

MyChart (Apex) conducts a search for patients based on the study’s inclusion and exclusion criteria. This is a completely computer-aided search, meaning the computer—and not a person-- searches patient charts. When a patient is identified as potentially eligible, they receive an email from MyChart that says to log in to MyChart to read about a study they might be interested in. The email is short and is the same for every recipient—there is no patient-specific, study-specific or disease information in it.

When the patient logs into MyChart, there is a new “Research” tab with template information about participating in research and how to opt out of receiving recruitment messages. Then, the patient can click through to learn about a specific study they may be eligible for.

The patient has the option of clicking a link/button to let the study team know that they are interested in learning more about the study. Only if the patient takes this action will the study team receive information about the patient. If the patient clicks “No thanks” or simply does not respond, they will not be contacted by the study team, they won’t receive any follow-up emails from MyChart about this study, and their information will not be shared with the study team.

Consent Process:

| \| **Prior to eligibility determination (phone screening):**  In order to determine a subject's eligibility, a phone screening will be conducted. We will obtain verbal consent, as in-person consenting is not an option. Verbal consent is obtained by trained phone screeners. Verbal consent for phone screen is part of the phone screen itself.  **Prior to enrollment:**  After determining the subject is preliminarily eligible and prior to enrolling them in the study, the subject will receive consent documents by mail (with post-marked return envelope) or/and e-mail.  In a separate phone call or zoom meeting, trained research staff will obtain consent and go over the various sections of the consent documents, ensuring that the subject has comprehended the consent documents and does not have any questions. Participants will sign consent via docusign or mailed forms. \| \| --- \| |
| --- | --- |

Only trained study staff will be obtaining consent from participants. These study staff will have gone through training with either the PI or the study coordinator. Training includes but is not limited to becoming familiar with consenting guidelines, mock consent practice, etc.

The study team will engage the potential participant in a dialogue, using open-ended questions about the nature of the study or the experimental treatment, the risks and benefits of participating, and the voluntary nature of participation. Potential participants will be asked or shown a series of questions to assess their understanding of the study purpose, procedures, risks and benefits, as well as the voluntary nature of participation (especially appropriate when the consent process happens online or through a mobile health app).

No information will be collected prior to any form of consent. To determine eligibility over the phone, information on MRI contraindications, general mental health, and physical health will be obtained to assess whether someone can complete the study. All information obtained before informed consent can be seen in the Eligibility Phone Screen, attached in Other Study Documents. All of the health information collected is necessary to determine eligibility. Because this information is collected prior to an in-person consent for eligibility purposes, a verbal consent will be obtained.

All data collected for eligibility purposes is collected via VA RedCap or Qualtrics and will remain electronic throughout the course of the study. While this data will not be used for analysis, it will be preserved as it is used to contact potential future participants (upon their consent to do so). All retained data collected is behind the secure UCSF firewall.

Subject identifiers will be kept separately from the research data in locked cabinets and locked office at the UCSF Osher Center.

Risks and Benefits:

Data are password-protected and stored on secured UCSF PHI drive, only accessible on UCSF server. The computers will be checked regularly for proper and safe operation. Identifiable information is also stored as a hard copy in a locked office and locked file cabinet. Subjects will be carefully screened and subsequentially informed about the fact that the principal investigator will be available at all times during the experiment. Subjects are informed that they may end the test session at any time and that participation in this research is voluntary.

Subjects are told that all information obtained is completely confidential and that their medical treatment at UCSF or the VA will not be affected, whether or not they choose to participate in this study. Coded numbers are assigned to each file in the data base to ensure patient privacy. To minimize the risk that sensitive subject information may be disclosed, all subject information will be kept in locked cabinets or in databases with secured passwords.

Records and data will be rigorously protected. Examiners will be clinically trained and sensitive to signs of stress, anxiety, or fatigue so that testing will be immediately terminated should any subject experience signs of discomfort. Any incidental findings regarding subjects' health will be submitted to his/her physician at subjects' request.

**Risk management procedures associated with sensory function testing:**The subjects will be familiarized with the sensory testing procedures prior to testing. Subjects will receive various levels of painful and nonpainful stimuli and will be asked whether they would like to participate in this study. This will give the subject the opportunity to experience the level of painful stimuli that will be applied and to decide whether he/she wants to continue participating in the study. The sensory tests may cause some pain and/or discomfort and/or temporary reddening of the skin. However, with the proposed stimulus parameters these stimuli will not damage the skin or subcutaneous tissue. We maintain that this is a minimal risk, non-invasive procedure which is not known to produce adverse effects. Indeed, the 15 years that [name] has been doing this procedure, there have been no adverse effects. Thus, we believe this is justification for classifying this as a minimal risk study. Subject are allowed to end participation if their perceived pain from thermal procedures is too great to tolerate.

**Reportable information:**Evidence of elder or child abuse, as well as threat to self or others, will be reported. Participants are notified of this in the verbal and in-person consents. If it is suspected that the subject is in danger of harming him/herself or someone else, or if child abuse or neglect or elder abuse has occurred, appropriate authorities will be notified as required by law.

**Self-report measures:** The main risks associated with these procedures are fatigue and irritability with the testing procedure. The investigator and research assistants are trained to frequently check the subjects about their willingness and ability to continue with the testing. If subjects express concerns about continuing with the testing, the investigator has instructed the research assistants to stop testing, offer a break, or, in case the subject is not willing to continue, to terminate the testing session. Overall, however, previous comparable studies have not resulted in any significant discomfort or anxiety expressed by the participating subjects.

**Risk management procedures associated with sensory/repeated heat/thermal grill stimulation:** The subjects will be familiarized with the thermal stimulations prior to testing. Subjects will receive various levels of painful and non-painful stimuli and will be asked whether they would like to participate in the study. This will give the subject the opportunity to experience the level of painful stimuli that will be applied and to decide whether he/she wants to continue participating in the study. The thermal grill and heat stimulation equipment will be regularly checked by the investigators for accurate temperature application so that the programmed temperature corresponds to the applied temperature.

**Risks associated with functional magnetic resonance imaging:**According to the FDA, there is currently no evidence that MRI with approved scanners of up to 7 Tesla signal strength are associated with adverse effects. moreover, other fMRI centers across the country are regularly using up to 7T MRI scanners for research purposes. However, there are two major sources of risk. First, the subject may experience discomfort being in the confined and sometimes noisy environment of the scanner. Second, the strong magnetic field will affect electronic, magnetic, and metal devices that subjects carry with them or that have been implanted in the subject's body. Additionally, female subjects capable of childbearing, will be asked a number of questions regarding their use of reliable contraceptive methods in order to be as sure as possible that they are not pregnant. Even though there are no known risks to an unborn child associated with fMRI, women of child-bearing potential who are not using reliable contraceptive methods will be excluded from this study.

**Data collection:**The risks involve some degree of loss of privacy. This will be minimized as much as possible, as described elsewhere in this application.

Information regarding drug/alcohol will be obtained via the attached eligibility phone interview, and ,may be considered embarrassing or may be illegal/stigmatized. Subjects are reminded that they are free to decline any questions that they are not comfortable providing a response for.

Reports of elder or child abuse, or indications of harm to self or others, will be reported and may result in criminal or civil liability.

Only designated study personnel included explicitly on the current IRB application will have access to any study records (both paper and electronic). No research results will be added to the patient's medical record unless medically necessary. Data will only be shared with those parties specified on the HIPAA form, which includes UCSF, UCSF IRB personnel, VA regulatory personnel, and the subject's primary care physician in the event of a medical complication.

Additionally, U.S.C 7332-protected sensitive information will be protected by the same rigorous standard as all other data. identifying information associated with this data will never be shared in reports or at conference proceedings, as with all other data.

Only designated study personnel included explicitly on the current IRB application will have access to any study records (both paper and electronic). No research results will be added to the patient's medical record unless medically necessary. Data will only be shared with those parties specified on the HIPAA form, which includes UCSF, UCSF IRB personnel, VA regulatory personnel, and the subject's primary care physician in the event of a medical complication.

Additionally, U.S.C. 7332-protected sensitive information will be protected by the same rigorous standard as all other data. Identifying information associated with this data will never be shared in reports or at conference proceedings, as with all other data.

VA research records will be retained within the VA-protected environment (e.g., VA server – please include the R Drive folder location/name, VA lab location, etc.), only accessible by authorized VA personnel, and disposed in accordance with the VHA Records Control Schedule (RCS 10-1). Any VA data shared with an external entity will be transmitted via FIPS 140-2-compliant encrypted methods as required per VA policy.

Financial considerations:

Subjects will be compensated for their time. Subjects will receive $100 per visit to the SFVAMC (2 visits = $200). They will receive $15 for travel reimbursement for each individual visit. Therefore, if a subject completes these 2 visits, they will receive up to $230 for SFVAMC visit compensation and travel compensation.

For the qualitative interview at the UCSF Osher Center, 20 of the 30 participants will receive $100 each and $15 for travel reimbursement.

For responding to the EMA, participants will receive $0.50 for each completed EMA assessment, up to $2.50 per day over 8 weeks (56 days), or up to $140 total.

Participants will be compensated a total of up to $485 for their participation in the study (inc. travel reimbursement).

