All instruments have been published. In parenthesis: (number of items), in brackets: *[reference],* measures used in REACH or IPRP studies are marked with *.

1) BACPAC Baseline Demographics*Includes HEAL required questions*(22)* only at baseline. This includes questionnaire items necessary to  adjust for MRI, e.g. to fit MRI-compatible correcting eye glasses.

2) PEG scale assessing pain intensity and interference (Pain, Enjoyment, General Activity) (3)*

3) Generalized Anxiety Disorder (GAD-2)*[Kroenke et al, 2007]*(2)*

4) Patient Health Questionnaire-2 (PHQ-2)*[Kroenke et al, 2003*[**(2)**](https://iris.ucsf.edu/Study_App.jsp?FORM_MODE=EDIT&tab=full&s=1701923559657#_ENREF_2)*

5) Tobacco, Alcohol, Prescription medication, and other Substance use (TAPS) tool (4)*

6) PROMIS Physical Functioning Short Form 6b (2 items not in PROMIS-29)*

7) PROMIS Sleep Disturbance 6a*[Yu et al, 2011]*(2 items not in PROMIS-29)*

8) Sleep Duration Question*[Kurina et al, 2013]*(1)*

9) Pain Catastrophizing Scale - short form 6 (PCS)*[McWilliams, 2015]*[**(6)***](https://iris.ucsf.edu/Study_App.jsp?FORM_MODE=EDIT&tab=full&s=1701923559657#_ENREF_6)

10) Patient Global Impression of Change (PGIC) (1) only at 8 weeks.

11) PROMIS-29+2 Profile v2.1 (PROPr) 02Jan2020 *[PROMIS]*(31)*

12) Charlson Comorbidity Index (CCI), *[MDCalc (*[*https://www.mdcalc.com/charlson-comorbidity-index-cci*](https://www.mdcalc.com/charlson-comorbidity-index-cci)*)]** baseline only
13) PainDETECT Questionnaire (PD-Q)*[Freynhagen et al., 2006]*(7)*

14) Fear-Avoidance Beliefs Questionnaire Physical Activity (FABQ-PA)*[Waddell et al., 1993]*(5)*

15) Chronic Pain Acceptance Questionnaire-SF8*[Fish et al. 2010]*(8)*

16) Multidimensional Assessment of Interoceptive Awareness (MAIA)*[Mehling et al., 2018]*(37)

17) Perceived Stress Scale*[Cohen et al., 1989]*(4)*

18) International Positive (and Negative) Affect Schedule 10-item SF*[Watson et al., 1988]*(5)*

19) PROMIS Emotional Support 4a V2*[Tucker et al, 2014]*(4)* only baseline

20) Pain Self-Efficacy Questionnaire 4-item version (items 4, 6, 8, 9)*[Chiarotto et al, 2016]*(4)*

21) Primary Care PTSD Symptom Screener*[Prins et al, 2016]* (1)* only baseline

22) Financial Strain*[Puterman et al, 2012]*(1)* only baseline

23) Perceived Discrimination *[NIMDH]*(1)* only baseline

24) Expectation of Pain Relief*[Cormier et al, 2016]*(1)* only baseline

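### The Non-Distraction entry limit of 2.91 is stated to be the reference mean plus one SD, which contradicts the protocol's below-average label and its claim to select habitual distraction

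*Protocol*

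**What the plan says.** Inclusion Criteria, item 6, names the target as "Low level of interoceptive awareness and habitual distraction as coping mechanism with pain" and defines it by two rules.

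- **6a:** "MAIA summary score below the population mean score of 3.41", the mean of a primary care sample from an earlier study.
- **6b:** a Non-Distraction score below 2.91 on a 0–5 scale. On its origin: "The value of 2.91 is the mean value plus standard deviation in the same sample".

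The same item says the rule was chosen to test the hypothesis in patients with "below average interoceptive awareness and preference for distracting themselves from their pain experience".

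Determination of Eligibility repeats both limits and the derivation ("the value of 2.91 is the mean value plus standard deviation in the same sample"). It then says that REACH enrollees have already met every criterion except one: "the below-average value of the MAIA summary and Non-Distraction scores".

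**The concern.** The protocol uses 6b as an upper limit to pick out people who distract themselves, so a low Non-Distraction score means more distraction. An upper limit one SD above the mean removes only the strongest non-distracters. Everyone between the mean and mean plus SD enters, although they distract themselves less than the average reference patient. For any SD above zero, the below-average label is therefore false for 6b, while it is correct for 6a.

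What is at stake is whom the results describe. The study has 30 participants and no control group, so the entry criteria largely define the population. If the report repeats the protocol's description, it will attribute a habit of distraction to a group in which that habit was hardly selected.

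**Working it through.** **Inputs from the protocol.** 6a limit = reference mean of the summary score (3.41). 6b limit = reference mean + 1 SD of Non-Distraction (2.91). Planned sample = 30.

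**Not in the protocol.** The reference Non-Distraction mean and SD, the correlation between the two scores, and the score distribution in screened patients with chronic low back pain. The figure 2.91 therefore cannot be rebuilt. The shares below need only its position relative to the mean, plus the assumptions named.

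**Step 1: 6b alone, normal scores.** P(X < mean + SD) = Φ(1) = 0.841. A limit at the mean would give Φ(0) = 0.500. Of those passing 6b alone, the share above the mean is (0.841 − 0.500)/0.841 = 0.406.

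**Step 2: does the 84% depend on normality?** A beta distribution on 0–5 with mean + SD fixed at 2.91 and an assumed SD of 0.5 to 1.2 gives 84% down to 81%. The one-sided Chebyshev (Cantelli) bound guarantees only 1 − 1/(1 + 1) = 50% for an arbitrary distribution. If the mean in screened patients lies 0.5 SD above or below the reference mean, the normal figure becomes Φ(0.5) = 69% or Φ(1.5) = 93%.

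**Step 3: 6a and 6b together.** Bivariate normal with assumed correlation ρ. Let J = P(summary < mean, Non-Distraction < mean + SD) and K = P(both < mean). The share of those admitted who are above the Non-Distraction mean is (J − K)/J.

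| ρ (assumed) | J | K | (J − K)/J | Of 30 |
|---|---|---|---|---|
| −0.3 | 0.392 | 0.202 | 0.486 | 14.6 |
| 0 | 0.421 | 0.250 | 0.406 | 12.2 |
| 0.4 | 0.459 | 0.315 | 0.313 | 9.4 |
| 0.6 | 0.478 | 0.352 | 0.263 | 7.9 |
| 0.7 | 0.487 | 0.373 | 0.233 | 7.0 |

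**Step 4: what 6b adds once 6a is met.** Since P(6a) = 0.5, the share that 6b then excludes is 1 − J/0.5. This is 16% at ρ = 0, and runs from 22% at ρ = −0.3 to 3% at ρ = 0.7.

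**The case against.** **The phenotype named in the hypotheses and aims is low interoceptive awareness, and 6a selects it.** This stands. Distraction enters only through the eligibility text. No listed hypothesis, aim or analysis concerns habitual distracters as such, so a reader who infers that the whole sample misses its phenotype goes too far.

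**The 84% is not the share of patients who enter the trial.** This also stands. It belongs to 6b alone in a normal reference sample. Both rules must be met, the reference is a primary care sample, and the share among screened patients is unknown.

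**Scoring above the reference mean is not the same as not distracting oneself.** This is fair, because the protocol gives no absolute threshold. One might point out that 2.91 exceeds the scale midpoint of 2.5, but that does not support the larger figures. With an assumed SD of 0.5 to 1.2 the reference mean is 2.91 − SD, or 2.41 to 1.71, already below the midpoint. Under normality and ρ = 0, 32% to 11% of those passing both rules would exceed 2.5 (24% to 5% for ρ between 0.4 and 0.6). The step 3 shares measure departure from the below-average label, not absence of distraction.

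**The lenient limit may be deliberate, or the words may be wrong rather than the number.** Either is possible. If 2.91 were in fact the mean, the selection problem would vanish. The derivation appears in two sections, which makes an isolated slip less likely but does not exclude one.

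**A reader might infer that the limits come from an older release of the questionnaire.** The sample cited in Determination of Eligibility dates from 2013, while Questionnaire Instruments lists a 37-item form with a 2018 reference. Two citation dates do not show that items or scoring differ, and the protocol says nothing on this.

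None of these points removes the contradiction between the stated derivation and the stated description.

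**Conclusion.** The point holds as an internal contradiction in an entry criterion, and that part needs no distributional assumption. Followed as written, 6b admits people above the reference mean on Non-Distraction and hardly selects for distraction.

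The size is illustrative. Under normality, about 84% of the reference sample pass 6b alone. Some 42–48% pass both rules at assumed correlations of 0 to 0.6, and 26–41% of those are above average on Non-Distraction, or about 8 to 12 of 30. Over assumed correlations of −0.3 to 0.7 the share is 23–49%, or about 7 to 15 of 30. No value in that range makes it negligible.

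The consequence is limited to whom the findings describe. Alpha, power, the feasibility outcome and the selection of low awareness by 6a are untouched. The documents do not show which of the number, the derivation or the label is in error.

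**What to change.** State the reference Non-Distraction mean and SD, and reconcile Inclusion Criteria item 6 with Determination of Eligibility. Cite the source consistently: the first section points to reference 4, which the list gives as a thermal-grill paper, and the second to reference 10. Then take one of two routes.

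- **If 2.91 is mean plus SD and is kept:** remove the below-average, habitual-distraction and preference-for-distraction wording for 6b. Describe the rule as excluding only scores more than one SD above the reference mean. Limit conclusions to patients with low interoceptive awareness, and report results descriptively for participants below the reference Non-Distraction mean. Cost: wording and one descriptive split, with no effect on recruitment. The subgroup will be small and its estimates imprecise.
- **If a below-average group is intended:** the limit has to be the reference mean. Cost: fewer eligible candidates and slower enrolment. Under the step 3 model at ρ = 0, the share of the reference sample passing both rules falls from 42% to 25%.

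In either case, add one sentence confirming that both limits apply to the 37-item form as it will be scored.
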